## Abstract

**Background:**

Generalized anxiety disorder (GAD) is one of the most common mental disorders among university students; however, many students go untreated due to treatment costs, stigma concerns, and limited access to trained mental health professionals. These barriers are heightened in universities in India, where there are scant mental health care services and severe stigma surrounding help seeking.

**Objective:**

To evaluate the feasibility, acceptability, and efficacy of Internet-based, or “online,” cognitive behavioral therapy (CBT)-based unguided and guided self-help interventions (using the programs GAD Online and Lantern, respectively) to reduce GAD symptoms in students with clinical and subthreshold GAD and, ultimately, reduce the prevalence and incidence of GAD among the student population.

**Methods:**

Students will be recruited via 3 colleges in Hyderabad, India, and referred for a campus-wide online screening. Self-report data will be collected entirely online. A total of 300 qualifying students will be randomized in a 1:1:1 ratio to receive GAD Online, Lantern, or to be in a wait-list control condition, stratified by clinical and subthreshold GAD symptomatology. Students will complete a postintervention assessment after 3 months and a follow-up assessment 6 months later, at which point students in the wait-list control condition will receive one of the programs. The primary outcome is GAD symptom severity at 3 months postintervention. Secondary outcomes include GAD caseness at 9 months, other anxiety and depression symptoms, self-efficacy, and functional measures (eg, sleep, social functioning) at 3 and 9 months, respectively. Primary analyses will be differences between each of the intervention groups and the wait-list control group, analyzed on an intention-to-treat (ITT) basis using mixed-design ANOVA.

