#### Eligibility

Eligible participants will be current students of the colleges, all of which are English medium, aged 18 or older who provide their email address, informed consent to complete the study, and meet criteria for clinical or subthreshold GAD. This age range was chosen because individuals younger than 18 require parental consent for participation in research. Based on self-report responses in the online survey, students are categorized into clinical, subthreshold, and asymptomatic for GAD. Those who meet DSM-V diagnostic criteria for GAD as measured by criterion-based scoring of the 4th edition of the Generalized Anxiety Disorder Questionnaire (GAD-Q-IV) [42] are classified as clinical, or more realistically,

“a probable diagnosis of GAD based on self-report.” To note, the diagnostic criteria did not change from DSM-IV to DSM-V, and therefore the GAD-Q-IV questions can still be used to assess DSM-V GAD criteria. Those who score 5.7 or above using dimensional scoring of the GAD-Q-IV but are not clinical are classified as “subthreshold.” All others are asymptomatic. It is also important to note that clinical diagnosis should be established using a clinical interview, which is not feasible in this study, thus the use of the self-report measures. Moreover, this study’s aim is not to provide diagnoses to students but rather to use gold-standard instruments to provide appropriate “matches” between students and available resources (ie, the research study or referral).

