### Details of the Measurements

#### Generalized Anxiety Disorder Questionnaire (4th Edition)

The primary outcome is GAD symptom severity as measured by dimensional scoring of the 4th edition of the Generalized Anxiety Disorder Questionnaire (GAD-Q-IV) [42]. GAD caseness, as measured by categorical scoring of the GAD-Q-IV, is a secondary measure. The GAD-Q-IV is a 9-item self-report measure designed as an initial screen for the presence of GAD based on the DSM-IV. The GAD-Q-IV showed 89% specificity and 83% sensitivity when compared to structured interview diagnoses of individuals with GAD, social phobia, panic disorder, and a nonanxious comparison group. The GAD-Q-IV has demonstrated good test-retest reliability in a college sample over a 2-week assessment, with 92% of the sample showing stability across time with respect to GAD diagnosis [42].

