#### Outcome Analyses

A 3 condition × time mixed-design ANOVA will be conducted to examine both primary and secondary hypotheses. Using a mixed-design ANOVA will test for differences between 2 or more independent groups while subjecting participants to repeated measures. The model is a type of mixed effect model, with the fixed effects factor being a between-subjects variable and the random effects factor being a within-subjects variable. Follow-up paired comparisons will be conducted to specifically assess if there is significant differential change in GAD symptoms between each active condition and control from the baseline to the postcondition and follow-up assessments. Within- and between-group effect sizes will be calculated using Cohen’s *d* (based on the pooled standard deviation), specifically contrasting each active condition with the control condition for the main outcome.

Primary analyses will be undertaken using an intention-to-treat (ITT) approach, including all participants randomized regardless of treatment actually received, program engagement, or withdrawal from the trial. Using a mixed model design will allow us to include participants with missing data, which is likely to occur in large Internet-based trials.

Study site will be included as a covariate as this might have an influential effect given that the 3 sites were selected primarily based on accessibility versus between-site comparability. If some sites have poor recruitment, the data will be combined.

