Another limitation is that the primary outcome measurement tool, the GAD-Q-IV, and the associated diagnostic thresholds have been normed in US university student populations but not in an Indian university student population. One implication is that the prevalence of the disorder could be mischaracterized due to diagnostic criteria being interpreted differently cross-culturally. For example, the DSM-IV GAD criterion that anxiety be “excessive” might lead to underdiagnosis of GAD in developing countries in which worry is less likely to be reported excessive in the presence of comparatively more severe life concerns [70]. Using dimensional versus categorical scoring of the GAD-Q-IV to both determine eligibility and monitor for change in symptomatology, this concern might be partially addressed. The cutoff point of 5.7 was found to be overly sensitive in the US college population [42], so it is a reasonable threshold above which to initially allocate interventions to those potentially in need but not currently accessing services. However, future and parallel research should focus on validating the assessment tools.

Another potential limitation is the fact that the two active conditions differ both by the degree of coaching support and the program used, which precludes this study from clearly deducing the additional, if any, benefit of guidance. However, the primary hypothesis is that the use of one or both of the active interventions will lead to a greater GAD symptom reduction than the wait-list control. If the unguided program is found to be both feasible to disseminate to this population and relatively effective, future controlled studies can evaluate the comparative benefit of guidance and conduct cost-benefit analyses of delivering unguided versus guided programs. The conditions under which it is more or less effective will also be explored (eg, it might be more effective for those with higher reported motivation who are more likely to complete more of the program). The primary initial aim is an evaluation of the feasibility and efficacy of the model of survey-linked-to-online-interventions to reduce the incidence and prevalence of common mental health disorders in defined Indian university populations**.**

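### GAD caseness is a binary outcome fixed by stratum at baseline, but the named analysis ignores the stratum and does not separate remission from onset; the stated population aim goes beyond the design

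*Protocol article*

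**What the plan says.** **Strata.** In the Eligibility section the clinical group is "Those who meet DSM-V diagnostic criteria for GAD as measured by criterion-based scoring" of the GAD-Q-IV. For the other group it says "Those who score 5.7 or above using dimensional scoring of the GAD-Q-IV but are not clinical are classified as" subthreshold. Randomisation is stratified on these two levels.

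**Outcome.** The section on the GAD-Q-IV states "GAD caseness, as measured by categorical scoring of the GAD-Q-IV, is a secondary measure". On its time point the abstract says "Secondary outcomes include GAD caseness at 9 months"; Table 1 collects it at 0, 3 and 9 months.

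**Analysis.** Under Outcome Analyses, a condition-by-time "mixed-design ANOVA will be conducted to examine both primary and secondary hypotheses". Site is the only covariate named there. Under Descriptive Analyses, outcome measures are summarised by arm and overall, and chi-square tests are named only for baseline comparisons. Under Mediator and Moderator Analyses, symptom level may be explored as a modifier of the effect on GAD symptoms; caseness is not mentioned.

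**Aims.** The abstract's objective is, ultimately, to "reduce the prevalence and incidence of GAD among the student population". The Limitations section describes the primary initial aim as evaluating the feasibility and efficacy of a model "to reduce the incidence and prevalence of common mental health disorders in defined Indian university populations". The Objectives and Hypotheses section is narrower: efficacy in students with clinical or subthreshold GAD.

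**The concern.** The stratifier and the outcome come from the same criterion-based scoring of the same questionnaire. Within a stratum, caseness can therefore move in only one direction from baseline: clinical students can remit and subthreshold students can convert. A caseness rate over both strata adds persistence in one group to onset in the other.

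The introduction argues for treatment and for prevention as two goals. Remission bears on the first and onset on the second, but no analysis is named that would report either. A mixed-design ANOVA also suits a yes/no variable poorly, the more so when that variable has no baseline variance within either stratum.

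The wording of the aims adds to this. If lower incidence and prevalence in a university population is the primary initial aim, a reader will look for a result that speaks to it, and caseness is the nearest outcome.

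**Working it through.** **1. The plan's own figure.** The plan requires 64 per group for d = 0.5, with SD 3.46 and a difference of 1.73 (3.46 × 0.5 = 1.73). The normal approximation, two-sided 5% and 80% power, gives 2 × (1.960 + 0.842)² / 0.5² = 62.8, so 63; the t-test version gives 63.8, so 64. The figure reproduces. It concerns the continuous score only; the plan gives no figure for caseness.

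**2. Baseline caseness.** By definition it is 100% in the clinical stratum and 0% in the subthreshold stratum.

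**3. Inputs for the illustration.**
- 100 students per arm and about 30% attrition, from Sample Size Estimation.
- Share clinical f = 8 / (8 + 17) = 32%, from the pilot survey. This is an assumption: it rests on 25 students counted before the trial's exclusions. A range of 20% to 50% is shown in step 6.
- All persistence and onset rates below are assumptions; the plan gives none.

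Per arm this means 32 clinical and 68 subthreshold students. After 30% attrition there are 22 (22.4) and 48 (47.6), or 70 in all.

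**4. What the pooled rate shows.** Pooled caseness = f × persistence + (1 − f) × onset.

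| Scenario | Control | Active | Gap |
|---|---|---|---|
| A. Persistence 60% v 40%, onset 10% in both | 0.32×0.60 + 0.68×0.10 = 26.0% | 0.32×0.40 + 0.68×0.10 = 19.6% | 6.4 points |
| B. Onset 20% v 10%, persistence 50% in both | 0.32×0.50 + 0.68×0.20 = 29.6% | 0.32×0.50 + 0.68×0.10 = 22.8% | 6.8 points |

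A is purely a treatment effect and B purely a preventive one, with nearly the same pooled gap. Effects can also cancel. Control persistence of 70% with onset of 15% gives 0.32×0.70 + 0.68×0.15 = 32.6%. An active arm with persistence of 40% and onset of 29.1% gives 0.32×0.40 + 0.68×0.291 = 32.6% as well.

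**5. What the stratum is worth to the pooled comparison.** With 70 per arm, the 95% half-width for two simple proportions is 1.96 × √[(p₁q₁ + p₂q₂)/70], where q = 1 − p. Replacing each pq by its average within strata, f × pq(clinical) + (1 − f) × pq(subthreshold), gives the stratum-adjusted version.
- A: √[(0.1924 + 0.1576)/70] × 1.96 = 13.9 points; adjusted, √[(0.138 + 0.138)/70] × 1.96 = 12.3 points.
- B: √[(0.2084 + 0.1760)/70] × 1.96 = 14.5 points; adjusted, √[(0.1888 + 0.1412)/70] × 1.96 = 13.5 points.

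**6. Precision within strata.** The half-width is 1.96 × √[(p₁q₁ + p₂q₂)/n].
- Remission, n = 22: 60% v 40% gives 1.96 × √(0.48/22) = 29.0; 50% in both gives 1.96 × √(0.50/22) = 29.5. So about 29 to 30 points.
- Onset, n = 48: 10% in both gives 1.96 × √(0.18/48) = 12.0; 20% v 10% gives 1.96 × √(0.25/48) = 14.1. So about 12 to 14 points.
- With 20% clinical (14 and 56 per arm) the same formulas give about 36 to 37 and 11 to 13 points. With 50% clinical (35 and 35) they give about 23 and 14 to 17 points.

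**7. The population aim.** Randomisation is within each college and takes only consenting students who screen positive. Asymptomatic students are not randomised, and no college serves as a comparison. A campus rate with and without the programmes is therefore not observed.

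**The case against.** The other side has a good case on several points.

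- *The text does not assign ANOVA to caseness.* The ANOVA is tied to hypotheses, and caseness appears in none of those listed under Objectives and Hypotheses. This stands as a matter of wording: the link rests on its status as a secondary outcome. But ANOVA is the only outcome method the article commits to, so the point is about the fit of what is stated and not merely about missing detail.
- *Pooling over strata is nowhere stated.* Correct. It is inferred from summaries by arm and overall, and from a model whose only named covariate is site.
- *A reader might infer that remission and onset cannot be told apart in this trial.* The documents do not support that. Stratum is known at baseline and caseness is collected at 0, 3 and 9 months, so both follow from a cross-tabulation. What is absent is a stated analysis.
- *A reader might infer that the pooled comparison is invalid, or that prevalence cannot be addressed at all.* That is also unsupported. Allocation is stratified on this variable, and comparing arms at follow-up is a valid comparison of prevalence among enrolled students. In scenarios A and B the pooled result would correctly show fewer cases; the two differ in mechanism, not in direction.
- *The abstract's goal is only long-term.* The word ultimately does soften it. The Limitations section does not soften its version in this way: it makes evaluating such a model the primary initial aim.
- *Estimates within strata would be imprecise.* True, as step 6 shows. This argues for intervals and modest claims, not for leaving the estimates out.

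**Conclusion.** The concern holds in a limited form. Caseness is a binary secondary outcome whose baseline value is set by the randomisation stratum. The analysis as written makes no use of that stratum and does not separate remission from onset. The arm comparison remains a valid statement about the prevalence of probable GAD among enrolled students.

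Under the illustrative rates, adjusting for stratum shortens the pooled half-width by about 1 to 1.6 points. Estimates within strata carry half-widths of about 29 to 30 points (remission) and 12 to 14 points (onset). These sizes rest on assumed rates, the pilot mix and 30% attrition. That a pooled rate does not separate the two flows does not depend on those rates.

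Campus-level incidence and prevalence cannot be estimated from this design, so the aim in the Limitations section is wider than the trial can answer. No stated figure is disputed, and the primary analysis of the continuous score is unaffected.

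**What to change.** 1. Analyse caseness at 3 and 9 months with a logistic model, or a logistic mixed model over both visits, including arm, stratum and site.
2. As secondary estimates, report remission among clinical students and onset among subthreshold students for each active arm against wait-list, as risk differences with 95% confidence intervals. State in advance that they are imprecise and are not meant to support separate significance claims.
3. Restate the primary initial aim in the Limitations section and clarify the abstract's objective, so that conclusions are limited to remission, onset and prevalence of probable GAD among enrolled students. Any wider effect on campus incidence or prevalence can be kept as a long-term hope that this trial does not test.

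The cost is a small extra analysis, some rewording and a narrower claim. No new data, visits or participants are needed.

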**Results:**

The study commenced in February 2015. The sample was recruited over a 3-week period at each college. The trial is expected to end in December 2015.

**Conclusions:**

This trial will be the first to evaluate the use of Internet-based CBT programs compared with a wait-list control group for the treatment of GAD among students in Indian universities. If effective, these programs have the potential to reduce the mental health care treatment gap by providing readily accessible, private, and cost-effective evidence-based care to students with GAD who do not currently receive the treatment they need.

**Trial Registration:**

ClinicalTrials.gov NCT02410265 http://clinicaltrials.gov/ct2/show/NCT02410265 (Archived by WebCite at http://www.webcitation.org/6ddqH6Rbt).

## Introduction

### Background

Anxiety disorders are the most prevalent class of mental health disorders across the world, with an estimated lifetime prevalence of 4.8-31.0% [1]. Generalized anxiety disorder (GAD), in particular, is one of the most common disorders. In a nationally representative sample in the United States, there was a 5.7% prevalence of GAD [2], and in 14,175 students across 26 United States college campuses, there was a 7% prevalence of GAD [3]. Comparably, in India, a meta-analysis of 13 psychiatric epidemiological studies (N=33,572) conducted in urban and rural India across all age groups yielded an estimated prevalence rate of 5.8% for GAD [4]. Similarly, Nair et al [5] found a 6.6% prevalence of GAD among adolescents in India. In Indian universities, in particular, Sahoo and Khess [6] found a 19% prevalence of GAD in 405 young male university students. These studies suggest that anxiety is a major public health concern, particularly in Indian students. Given that the global average age of onset of GAD is in adolescence and in early adulthood [1,5,7,8], university students are a vulnerable population.

If left untreated, GAD has been demonstrated to have a chronic course and persistent symptoms [9] and is associated with significant distress, disability, quality of life, and medical problems [10]. In addition, subthreshold GAD cases (ie, individuals with significant symptoms who do not meet the full diagnostic criteria for GAD) have also proven equally costly in terms of functional impairment, medically unexplained symptoms such as pain [11], quality of life [12], disability, and help seeking [13,14]. The presence of GAD symptoms even increases the cost of health care from twofold to greater than fourfold [15], with disorder severity positively correlated with total medical costs [16]. Furthermore, both GAD and subthreshold GAD are significant predictors of first onset of other anxiety, mood, substance-use, and impulse-control disorders [17,18]. Studies that have evaluated possible GAD risk factors suggest that subthreshold symptoms might predict onset of GAD [18-20]. Thus, reducing GAD symptomatology among young people and targeting both treatment and prevention have tremendous public-health significance, not least of which is the potential to mitigate ongoing disability and costs [21].

Unfortunately, the majority of affected young people do not receive treatment. Young et al [22] estimated that only 20% of young people in the United States receive adequate treatment. In university environments, students often do not seek treatment due to barriers such as time, stigma concerns, treatment cost, insufficient information about their disorder or available treatment [23,24], and particularly in India, confidentiality concerns [25]. Hunt and Eisenberg [23] discovered that students indicate a preference for self-management and the perception that issues are not serious enough to warrant treatment, and both these are considered primary reasons for not seeking help.

Such stigma around mental health may be a larger issue in Indian versus US populations. Among Asian cultures, research has documented a belief that “emotional reactions” do not merit professional intervention [26]. Another study among Indian adolescents documented a perception that having a mental illness is shameful [27]. Stigma may result in resistance to seeking treatment and those who might seek treatment may be reluctant for fear of discrimination. Online programs offer the advantage of reducing some aspects of stigma.

Even more impactful than the issue of low help seeking is a lack of treatment availability. In the United States, inadequate counselor availability is a significant issue [23]; in developing countries, the issue is significantly worse. In India, for example, there are only 5000 licensed mental health professionals; in the United States, there are 550,000 to treat a population one-fourth of India’s size [28]. This equates to roughly 1 professional per 580 individuals in the United States and 1 per 250,000 in India. There is, therefore, considerable opportunity to improve mental health treatment for students in India by increasing access to treatments that do not require mental health professionals to deliver them.

Internet-based, or “online,” self-help interventions have the potential to overcome barriers such as stigma, cost, and limited specialist services. Online, unguided and guided self-help interventions offer an opportunity to provide cost-effective, evidence-based care to a large population simultaneously [29]. Unguided, purely self-help (SH) interventions have proven efficacious for treating individuals diagnosed with anxiety disorders including GAD [30-36]. In one study, individuals identified as having clinical GAD received a fully automated SH program and achieved significant improvement across primary symptom severity measures as well as secondary measures such as self-confidence in managing mental health issues and quality of life [32]. Guided self-help (GSH) interventions, in which an online program guide or “coach” [37] supports and guides a user by monitoring progress in the program and providing personalized feedback and encouragement typically via messaging and/or phone, have proven even more effective [38,39]. In fact, GSH interventions have been demonstrated to be as effective as in-person therapy for treating clinical anxiety disorders [39] and depression [40]. These findings suggest that less costly, Internet-based SH and GSH interventions can be considered adequate alternatives to traditional in-person therapy. However, there is no research examining the efficacy of these interventions to reduce GAD symptomatology in students in Indian universities who currently have limited access to mental health care. Therefore, this study seeks to evaluate the feasibility, acceptability, and efficacy of Internet-based interventions, both unguided (using the GAD Online program) and guided (using the Lantern program), to reduce GAD symptoms in Indian university students.

